**Methods:**

A total of 120 participants aged 9–18 years meeting diagnostic criteria for VS will be recruited from the Anglia Ruskin University Eye Clinic. A widely used instrument, the Intuitive Colorimeter, will be used to select, for each participant, the chromaticity of precision tinted lenses (PTL) that they claim optimally alleviates their symptoms and a similar control colour will also be determined. Participants will be randomised into group 1, receiving spectacles with intervention A (optimal tint) followed by B (sub-optimal tint), or group 2, receiving the two interventions in the order BA. The first intervention will be used for 1 month, followed by a 1-month washout period, the second intervention for 1 month, and then a head-to-head comparison in the clinic with participants invited to keep their preferred pair of spectacles. The primary outcome measurement is symptoms (measured by symptom diaries and symptom questionnaires); the secondary outcome measure is observed school performance (measured by academic behaviour surveys); and the tertiary outcome measure will be reading speed (measured by the WRRT).

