## Design and methods

This will be a single-centre, double-masked randomised controlled crossover trial. There will be a 50:50 allocation ratio to evaluate the superiority of a hypothetically optimal intervention over a sub-optimal intervention.

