### Sample size

A sample size ($$n$$ = 120) was determined based on the sample size calculation for AB/BA crossover trials described by Jones and Kenward [39]:$$n=\frac{2{({Z}_{1-\beta }+{Z}_{1-\alpha /2})}^{2} {\sigma }_{\omega }^{2}}{{\mu }_{d}^{2}}$$where:$$n$$ = total needed sample size$$({Z}_{1-\beta }+{Z}_{1-\alpha /2})$$ = sum of $$z$$-scores at which the tails of the normal distribution correspond to probabilities $$\alpha$$ and $$\beta$$, where $$\alpha$$ is the desired significance level for hypothesis testing, and $$1-\beta$$ is the desired power of the test$$\sigma$$ = within-subjects standard deviation of symptom scores$${\mu }_{d}$$ = mean difference in scores between control and experimental conditions $$({\mu }_{ctrl}- {\mu }_{expt})$$

This total sample size estimate was calculated using an effect size of half a standard deviation (0.5 SD), 90% power, a 0.05 probability of a type I error ($$n$$ = 88), and an allowance for individuals who might withdraw from the study.

To establish whether an experimental treatment is superior to the control, the convention is to set the significance level (*α*) at 0.05, as recommended by Julious [40]. Furthermore, a statistical power of 0.90 (*β*= 0.10) was selected, as this is the recommended standard for crossover trials [39, 40].

When discussing the effect size for this RCT, it was apparent that there are no prior data to aid the selection of effect size, and this RCT is proposing a new outcome measure. Therefore, it was necessary to investigate existing statistical rationales to assist with this decision. An effect size (standardised mean difference) of 0.5 SD was chosen based on Lakens [41] and Norman et al. [41, 42].

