Initially, all data will be checked by scatter plots of raw data. All data will be tested for normality using the Shapiro-Wilk test, and non-parametric data will be transformed to parametric where possible. Simple comparisons will use paired *t*-tests, or the Wilcoxon signed-rank test as appropriate. For more complex analyses, a Mixed-Effects Model for Repeated Measures (MMRM) will be carried out to account for the crossover design, including fixed effects (intervention type, period, and sequence) and random effects (participant variability).

A confirmatory check will be performed to test for order effects (e.g. whether participants who have the optimal tint after the sub-optimal tint have a statistically different outcome from those who have the sub-optimal tint after the optimal tint). If such an effect is found, key analyses will be repeated whilst controlling for the order effect. In addition, an analysis of the effects of the first tint alone will be compared across participants. The analysis will have low power and will be confirmatory, but it is independent of order effects.

Participants for whom there is a complete set of symptom diary data for at least 2 weeks of wear with both interventions will be analysed on an intention-to-treat basis (ITT) [44]. In the unlikely event that any participants are misallocated, then key analyses will also be run according to a per protocol approach. For the symptom questionnaire conducted before enrolment in the trial and for the academic behaviour surveys, data will only be analysed for participants for whom data are available for *both*interventions [44].

Sensitivity analysis will also be carried out to confirm the robustness of the data produced.

The secondary outcome survey measures will be converted to numeric values. Scores will be aggregated and averaged across surveys and then prepared for statistical analysis using the approaches described above. Tertiary outcome measures will be assessed separately as an exploratory analysis. Tertiary outcome measures will undergo reliability testing using the intraclass correlation coefficient, and analysis for order effects using repeated measures ANOVA, before comparing interventions using standard *t*-tests.

All statistical analyses will be conducted using R (version 4.3.1, R Core Team 2023).

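### The conditional repeat analysis for order effects cannot address carry-over, and period adjustment should not wait for a significant check

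*Protocol article*

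**What the plan says.** The trial is a two-period, two-sequence crossover. Its abstract describes the two arms, the first of them "receiving spectacles with intervention A (optimal tint) followed by B (sub-optimal tint), or group 2, receiving the two interventions in the order BA". On timing, the same abstract says: "The first intervention will be used for 1 month, followed by a 1-month washout period, the second intervention for 1 month".

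Under Statistical methods for primary and secondary outcomes (Protocol article), four elements bear on order:

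- Simple comparisons use paired t-tests or Wilcoxon signed-rank tests. These contain no period term.
- More complex analyses use a mixed model "including fixed effects (intervention type, period, and sequence) and random effects (participant variability").
- Next comes a test of order: "A confirmatory check will be performed to test for order effects". The example given compares participants who had the optimal tint second with those who had it first. The consequence is: "If such an effect is found, key analyses will be repeated whilst controlling for the order effect".
- Whatever that check shows, the first tint alone is compared between participants. The section says this analysis has low power and does not depend on order.

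Order effect is not defined beyond the one example, and the article does not use the term carry-over.

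**The concern.** Order effect can mean two things in an AB/BA trial, and they call for different handling.

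A **period effect** is a shift between the first and second wearing month that applies to both tints, such as a school holiday or fatigue with the diary. It can be estimated and removed by a period term.

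**Differential carry-over** is the first tint influencing the second period by an amount that depends on which tint it was. With two periods and two sequences it cannot be separated from a sequence difference or a treatment-by-period interaction. No sequence or period term removes it from the tint estimate.

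The example in the plan is a between-sequence comparison, which is the carry-over contrast. The prescribed response, controlling for it, would leave the tint estimate where it was. A positive check could then be reported as order having been controlled, and a negative one as order having been ruled out; neither would be justified. If a period effect is meant, the adjustment is legitimate, but a preliminary significance test then decides whether it is applied.

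**Working it through.** **Inputs.** From Sample size: effect 0.5 SD, two-sided alpha 0.05, power 90%, n = 88 before the withdrawal allowance, 120 with it. The SD is defined there as the "within-subjects standard deviation of symptom scores". From Design and methods: 1:1 allocation. Assumed, because the article gives no values: the size of carry-over λ, the period effect p, the between-period correlation ρ, and how completers split by sequence. All effects below are in within-participant SD units (σ_w = 1), with a positive tint effect meaning benefit.

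**The plan's own figure.** n = 2(1.2816 + 1.9600)² / 0.5² = 2 × 10.507 / 0.25 = 84.06, so 85. Rounding up to a multiple of the block size of 4 gives 88. That explanation is inferred, but the figure is reproduced closely enough to use 44 per sequence.

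**Bias from carry-over.** Let τ be the tint effect and λ the carry-over of the optimal tint minus that of the sub-optimal tint. The expected period 1 minus period 2 differences are:

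- AB: τ − p − λ
- BA: −τ − p

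Half the difference between them is τ − λ/2. The period effect cancels and half the carry-over remains. With τ = 0.5:

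| λ (assumed) | Mean estimate |
|---|---|
| 0.1 | 0.45 |
| 0.25 | 0.375 |
| 0.4 | 0.30 |
| 0.5 | 0.25 |

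Over 4,000 simulated trials of 88 participants, the mean estimates were 0.375 for λ = 0.25 and 0.251 for λ = 0.5.

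**Effect of the control.** Sequence is a between-participant term, so with complete pairs it cannot alter a within-participant estimate. In one simulated data set (44 per sequence, λ = 0.5, p = 0.2, ρ = 0.5):

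| Model | Tint estimate | SE |
|---|---|---|
| Intervention | 0.131 | 0.163 |
| + period | 0.131 | 0.157 |
| + period + sequence | 0.131 | 0.157 |

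The value 0.131 is a single draw around the expected 0.25. What matters is that it does not move. Period changes the SE; sequence changes neither figure.

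**Power of the check.** The sequence test compares participant totals. Their difference is λ and their SD is √(4σ_b² + 2), where σ_b² = ρ/(1 − ρ).

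- ρ = 0.5: SD = √6 = 2.449; SE = 2.449 × √(2/44) = 0.522. Power is about 12% for λ = 0.4 and 16% for λ = 0.5.
- ρ = 0.7: σ_b² = 2.333; SD = √11.33 = 3.367; SE = 0.718. Power is about 9% and 11%.

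**Period effect in the paired tests.** The optimal minus sub-optimal difference has expectation τ − p in AB and τ + p in BA, ignoring carry-over. The unadjusted mean is therefore τ + p(n_BA − n_AB)/n. With equal completers the period term vanishes. With an assumed 50/38 split it is −12/88 × p = −0.14p; for p = 0.2 that is −0.027. A test for that period effect has SE = √2 × √(1/50 + 1/38) / 2 = 0.152, so 0.2/0.152 = 1.31 and power is about 26%. A conditional rule would usually leave this bias in place.

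**First-tint comparison.** This is free of carry-over: its simulated mean stayed between 0.496 and 0.503 in every scenario. Its power for 0.5 SD at n = 88 is about 65%, 38% and 18% for ρ = 0, 0.5 and 0.8. If it were looked at only when the sequence test rejected, its mean would be 0.92 (λ = 0.25) or 0.87 (λ = 0.5) against a true 0.5. It must therefore stay unconditional, as the plan now has it.

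**The case against.** The strongest defence is that the plan promises less than a critic might infer. A reader could conclude that the article claims the repeat removes carry-over, or that it is the trial's only safeguard. The text supports neither. It never says that carry-over is removed. It already plans the first-tint comparison without any condition and discloses its low power. The mixed model already holds period and sequence, and there is a 1-month washout. All of this stands.

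Nor can it be said that the repeat has no effect at all. For the paired tests, adding period changes the SE and, with unequal completers, the estimate. Unequal completers are plausible: the plan recruits 120 to end with 88, and analyses the diary only in participants with data under both tints.

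The size of carry-over is also unsupported. A λ of 0.4 against an effect of 0.5 means 80% of the benefit persisting through a month without the lenses, and nothing in the article suggests that. Persisting benefit of the optimal tint would pull the estimate towards the null, so it would cost power and would not create a false claim of benefit.

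Finally, the exact model for an order check is often left to an analysis plan. That has limited force here, because the article does fix a rule and gives a sequence contrast as its example. The section also recommends the first-tint analysis for not depending on order. That rationale fits carry-over better than a period effect, since a period effect would not require setting the second period aside.

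**Conclusion.** The point holds in a limited form. The test-then-control rule cannot address carry-over, which is what its own example tests for, and under the period reading it makes conditional an adjustment that should always be made. The algebra (bias of half the carry-over, unaffected by a sequence term) needs only the AB/BA layout and complete pairs. The sizes rest on assumptions: carry-over of 0.1 to 0.5 for a mean estimate of 0.45 to 0.25, correlation 0.5 to 0.7 for the power of the check, and a 50/38 split for the 0.14p bias in the paired tests. The article gives no evidence that carry-over will occur, and it does not leave the trial without protection against it. The damage to prevent is a report that order was controlled or excluded when the analysis could show neither, together with an avoidable small bias if unadjusted paired tests carry the main result.

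**What to change.** In the statistical methods section:

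1. Define order effect, separating period effect from carry-over.
2. Delete the test-then-control step.
3. Make the mixed model with intervention, period and sequence the unconditional primary analysis, with the paired tests supportive only.
4. Report the sequence estimate with its confidence interval as description, with no decision attached.
5. Keep the first-tint comparison as planned, as the carry-over-free sensitivity analysis that does not depend on any test.
6. State that protection against carry-over rests on the 1-month washout.

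The cost is a little rewording and one more estimate to report. The sample size and visits do not change, and the Trial status section says recruitment has not begun.

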### Criteria for discontinuing or modifying allocated interventions

If a participant considers the dispensed spectacle frames are unsuitable or uncomfortable, they can return to the researcher for frame adjustment or dispensing of more appropriate frames. In this scenario, the lens interventions will not be changed.

If a participant experiences aversion or discomfort with one of the interventions, they can stop wearing the PTLs but will be asked to record reasons in the symptom diary. Participants will have previously worn any new optical prescription for 1 month before entering the trial to ensure that there is no non-tolerance to the optical prescription (see Additional file 1).

The participant can remain in the trial, regardless of how much they wear their PTLs, as long as symptom diaries are completed. Written and verbal communication will be provided to participants explaining this when the spectacles are dispensed.

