### Adverse event reporting and harms

The risks of harm are very low, and there is no ophthalmic drug intervention. Full optometric testing, which is a key part of this clinical trial, involves tests widely used in routine optometric practice. PTLs are designed to reduce symptoms of visual stress and improve reading speed. However, in the unlikely event that there is a marked increase in symptoms or reduced reading performance, affecting behaviour or academic outcomes, the participants can stop wearing the PTL and drop out of the trial. There have been no studies showing this effect.

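### The first-tint comparison needs only month-1 data, but the stated diary and survey analysis sets require data under both tints and make no exception for it

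*Protocol article*

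**What the plan says.** All the analysis text is in the protocol article, *Statistical methods for primary and secondary outcomes*. After the check for order effects, the plan adds a parallel-group look at the first period: "In addition, an analysis of the effects of the first tint alone will be compared across participants". Its justification is: "The analysis will have low power and will be confirmatory, but it is independent of order effects".

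The paragraph that follows sets out who is analysed:

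- **Diary (first primary outcome).** Participants with a "complete set of symptom diary data for at least 2 weeks of wear with both interventions will be analysed on an intention-to-treat basis".
- **Academic behaviour surveys.** The rule is that "data will only be analysed for participants for whom data are available for" both interventions.
- **Symptom questionnaire.** It shares the survey sentence, but the wording there refers to the questionnaire given ahead of trial entry. The set for the end-of-period questionnaire, the second primary outcome, is therefore unclear.
- **Any other set.** "In the unlikely event that any participants are misallocated, then key analyses will also be run according to a per protocol approach". This does not bring back children who have one period only.

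No set is named for the first-tint comparison, and neither rule is said to be limited to the paired comparisons.

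The article foresees losses. Under *Criteria for discontinuing or modifying allocated interventions*: "If a participant experiences aversion or discomfort with one of the interventions, they can stop wearing the PTLs". Under *Adverse event reporting and harms*, if symptoms worsen markedly or reading performance falls, "the participants can stop wearing the PTL and drop out of the trial". The *Discussion* lists attrition as a limitation.

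**The concern.** A first-period comparison is useful in a crossover trial because it compares groups formed by randomisation on data recorded before any second treatment. That protection depends on keeping everyone who has first-period data. If inclusion also requires usable data under the second tint, it depends on washout, fatigue with the diary and the reaction to the second tint. The last of these differs between the two sequences by design.

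At stake is the plan's only between-group check that is free of carry-over by construction. Read literally, the stated sets would discard observed first-month results, reduce power that the plan already calls low, and open the check to selection that randomisation does not control. The cause would be the analysis set, not missing first-month data.

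**Working it through.** **Inputs from the article** (*Sample size*, *Design and methods*): two-sided alpha 0.05; power 90%; effect 0.5 SD, with the within-subject SD (σw) in the formula; 88 before and 120 after the withdrawal allowance; 1:1 allocation in blocks of 4.

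**Assumptions, not in the article:** within-child correlation ρ; the timing of losses; how leaving depends on first-month symptoms.

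**1. The plan's own figure.** n = 2(z₀.₉₀ + z₀.₉₇₅)²σw²/μd² with μd = 0.5σw gives 2 × (1.2816 + 1.9600)²/0.25 = 84.06. Rounded up to a multiple of the block size this is 88, where non-central-t power is 0.906. The 88 is not in dispute. The implied allowance is (120 − 88)/120 = 26.7%.

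**2. Power of the first-tint comparison under random loss.** A single-period score has between-child SD σw/√(1 − ρ), so the standardised difference is d = 0.5√(1 − ρ). At ρ = 0.5, d = 0.354. Two-sample t-test power at that d:

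| Children analysed | Power |
|---|---|
| 60 + 60 (all have month-1 data) | 48% |
| 52 + 52 (half of the 32 losses fall before month 1 ends) | 43% |
| 44 + 44 (both-tints set) | 37% |

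For 60 + 60 against 44 + 44, the figures are 62% against 49% at ρ = 0.3, and 32% against 25% at ρ = 0.7. Under random loss the expected difference is unchanged, so only precision is lost.

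**3. Loss that depends on first-month symptoms in the same way in both sequences.** Large-sample simulation: true difference 0.50σw, ρ = 0.5, 26.7% lost, all after month 1, logistic dropout on the first-month score.

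| Odds of leaving per total SD worse | Difference in those kept (σw) | Shrinkage | Power |
|---|---|---|---|
| 1.6 | 0.48 | 4% | 36% |
| 2.7 | 0.43–0.44 | 13% | 33% |
| 4.5 | 0.39 | 21% | 31% |

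The shrinkage is nearly the same at ρ = 0.3 and 0.7. The sub-optimal-first group loses slightly more of its worst scores, which pulls the groups together.

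**4. Loss that depends on symptoms differently by sequence.** Same ρ and overall loss, with a log-odds slope of 0.5 per σw.

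| Mechanism | No true effect: bias, rejection rate | True effect 0.50σw: estimate |
|---|---|---|
| Random loss | about 0, 5% | 0.50 |
| Same dependence in both sequences | about 0, 5% | 0.47 |
| Sequence alone | about 0, 5% | 0.50 |
| Milder symptoms raise loss, optimal-first only | 0.25σw, 13.9% | 0.23 |
| Opposite directions in the two sequences | 0.50σw, 38.6% | 0.01 |

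In every row, using all first-period data gives an estimate at the true value and, with no true effect, about 5% rejection. The last two mechanisms work against the optimal tint; their mirror images would favour it.

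**The case against.** The strongest reply is that the contradiction is read out of silence. The both-interventions conditions suit the paired tests and the A-versus-B contrasts. They have no function in an analysis of one period, and no sentence ties them to it. A sensible analyst might use first-tint data for a first-tint analysis, and the set for a supportive analysis is often left to a fuller document. This stands in part: the rule is not expressly applied to the comparison. But the article does not leave the sets open. It states them directly after the first-tint analysis, uses the word only for the surveys, and makes no exception.

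A reader might go further and infer that the comparison is simply not independent of order. The document does not support that. First-month scores are recorded before any second tint is worn, so the scores kept carry no order or carry-over effect. What is lost is the guarantee against order-related selection. Bias arises only if leaving depends on outcome, and with no tint effect there is none even then unless that dependence differs by sequence. Nothing in the article indicates such a mechanism.

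A reader might also count the end-of-period questionnaire among the sets requiring both tints. Its sentence does not say that clearly, so the point is firm for the diary and the surveys only.

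Finally, the practical effect is modest. Even with all 120 children, power is about 48% at ρ = 0.5, so a null result would say little under either set. The plan already admits low power.

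**Conclusion.** The point holds as a conditional one. If the both-interventions rule is applied as written to the diary and the surveys, children with a complete first month are removed because of later events. The comparison is then no longer assured to be of the randomised groups or free of order-related selection.

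The certain cost is precision: at most about 11 percentage points of power at ρ = 0.5 (48% to 37%), or about 6 (43% to 37%) if half the allowance is lost before month 1 ends. The possible cost is bias: 4% to 21% shrinkage under the common dropout slopes assumed, and more in either direction if dropout depends on symptoms differently by sequence. All of these rest on an assumed correlation, loss pattern and dropout slope, none of which the article gives.

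Severity is low, because the analysis is supportive and the primary paired comparison is not affected by this point.

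**What to change.** In *Statistical methods for primary and secondary outcomes*, state that the requirement for data under both interventions applies to the paired comparisons only. Add that the first-tint comparison includes every randomised participant with first-period data on the measure concerned, grouped by randomised first tint, whether or not second-period data exist. In the same edit, say which set applies to the end-of-period questionnaire.

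The cost is a few lines of text and no new data. The first-tint and paired analyses will have different denominators, which the report should show. According to *Trial status*, recruitment has not begun, so the change can be fully prespecified.

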### Intervention description

The proposed double-masked RCT has five phases (Fig. 1). For a more detailed account of the procedure, please see Additional file 2.Participant recruitment follows three stages (see Additional file 2).Colorimetry, WRRT, and prescribing PTL interventions. Participants will be randomly allocated (with masking) to wear first either optimal (active) colour or sub-optimal (control) colour.Short-term effects of the first pair of PTL:Wilkins Rate of Reading Test (WRRT) at dispensing of first pair (first PTL vs no tint): The test will be administered (following test instruction manual) twice in each condition in the order ABBA with random allocation of PTL or no tint to A or B.Symptoms with the first pair from diaries (see Additional file 5) throughout 1 month of wear and a questionnaire at the end of the month.Academic behaviour survey completed by parents and teachers (see Additional file 6) in the last week of 1 month of wear.After a washout period, each participant will crossover to the other pair, and the researcher will assess the short-term effects of the second pair of PTL, as described in (3) above, including WRRT with second PTL vs no tint in ABBA order.After both pairs have been worn, participants will return for:WRRT with first PTL vs second PTL in ABBA order with random allocation to A or B.The researcher (maintaining masking) will compare symptom diaries from (3) and (4) and WRRT data to decide with the participant about the preferred pair to be dispensed to participants who wish to keep one pair.

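### The set labelled intention-to-treat is a complete-pairs set chosen after randomisation, so the tint contrast is open to bias if loss depends on symptoms or tint.

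*Protocol article*

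**What the plan says.** The section on statistical methods for primary and secondary outcomes defines the analysed participants by diary data: "Participants for whom there is a complete set of symptom diary data for at least 2 weeks of wear with both interventions". It states that they "will be analysed on an intention-to-treat basis (ITT"). A per-protocol analysis is foreseen only for misallocation. A sensitivity analysis is announced without content.

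For the other instruments the same section says: "For the symptom questionnaire conducted before enrolment in the trial and for the academic behaviour surveys, data will only be analysed" only where both interventions have data.

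Two other sections bear on who is lost:

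- Criteria for discontinuing or modifying allocated interventions: a participant with aversion or discomfort may stop, in that "they can stop wearing the PTLs but will be asked to record reasons in the symptom diary". It adds: "The participant can remain in the trial, regardless of how much they wear their PTLs, as long as symptom diaries are completed".
- Adverse event reporting and harms: after a marked increase in symptoms or reduced reading performance, "the participants can stop wearing the PTL and drop out of the trial".

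The intervention description uses the phrase on wear as the name of the treatment period: "Symptoms with the first pair from diaries (see Additional file 5) throughout 1 month of wear".

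**The concern.** An intention-to-treat set is fixed by randomisation. This one is fixed by diary completeness in both periods, which is known only afterwards and may itself respond to the tint. A participant who leaves in the first period, or before two diary weeks in the second, contributes nothing to the paired contrast. The harms section ties one such exit to worse symptoms, which is the primary outcome.

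The protocol's own background section notes that attrition in the 1994 crossover trial may have inflated the apparent benefit. The discussion concedes an attrition risk here too. If loss differs by symptoms or by tint, the primary result would be reported as intention-to-treat while carrying the same weakness. The allowance for withdrawals protects power but does nothing against selection.

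The second primary outcome has no clear set at all. The both-interventions rule names a questionnaire completed before enrolment, which cannot have data under two interventions.

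**Working it through.** **The plan's own figure.** The sample-size section gives n = 2(z₀.₉₀ + z₀.₉₇₅)²σ²/μ², with μ/σ = 0.5. This is 2 × (1.2816 + 1.9600)² / 0.25 = 84.06, which is 86 for equal sequences and 88 as a multiple of the block size 4. The stated 88 reproduces. Going from 88 to 120 allows a loss of 32/120 = 26.7%. Power by the noncentral t distribution for an undistorted effect of 0.5 is 0.970 at 120 participants, 0.906 at 88, 0.878 at 80 and 0.841 at 72. Sample size is not the problem.

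**Who is lost, by reading of the wear phrase.**

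| Participant | Phrase means days actually worn | Phrase names the period |
|---|---|---|
| Leaves before two diary weeks on either tint | out | out |
| Stops wearing early, keeps the diary | out | in |
| Stops after two full weeks, diary complete to then | in | in |

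The first row holds on either reading. The second is an ambiguity that the document does not settle.

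**Size of the possible bias.** All stopping figures below are assumptions. Score on the optimal tint = u + e − τ. Score on the sub-optimal tint = u + e. Every SD is 1. The chance of stopping in a period has log-odds logit(p) + slope × score, where p is the stopping chance at an average score. A stopper's period is removed, and a pair is kept only if neither period is stopped. The estimate is the mean difference (sub-optimal minus optimal) in kept pairs.

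True effect τ = 0.50:

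- Equal 5%, slope 0: estimate 0.499, 108 of 120 pairs kept. No bias.
- Equal 5%, slope 1: 0.476, 102 kept. Attenuation (0.500 − 0.476)/0.500 = 4.8%.
- Equal 10%, slope 1: 0.465, 90 kept. Attenuation 7.0%.
- Equal 15%, slope 1.5: 0.430, 76 kept. Attenuation 14%.
- 5% on optimal and 20% on sub-optimal, slope 0: 0.50, with 120 × 0.95 × 0.80 = 91 kept. No bias.
- 5% and 20%, slope 1: 0.35, about 83 kept, power 65%. Attenuation (0.50 − 0.35)/0.50 = 30%.

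No true effect:

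- Equal 5% or 10%, slope 1: estimate 0.00, false-positive rate 5%.
- 5% and 20%, slope 1: about −0.12, false-positive rate 13% to 14%. Reversing the two rates gives about +0.12, in favour of the optimal tint.

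If stoppers go on completing the diary and are counted, the estimate is 0.50 and there is no selection.

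**Does the mixed model repair it?** In the 5%/20%, slope 1 scenario with stoppers' periods missing, a mixed model that adds single-period data (variances taken as known) gives 0.28, against 0.35 for complete pairs. With no true effect it gives −0.18 and a false-positive rate of 21% to 23% across runs, against about −0.12 and 13%. Data in that scenario are not missing at random, so the model alone does worse. The gain comes from keeping diary data after wear stops.

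**The case against.** The strongest reply is that little is actually lost. Elsewhere the protocol uses its wear phrase as a label for the period. The section on discontinuing interventions also keeps non-wearers who fill in the diary. On that reading a person who dislikes a tint stays in the analysis. This stands, so a reader who infers that everyone stopping a badly tolerated tint is removed goes further than the text. It does not rescue the label, because people who leave are lost on either reading.

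Three further inferences are tempting and not supported:

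- That the discontinuation and harms sections contradict each other. Both are permissive: one says a participant can remain, the other that a participant can leave.
- That the diary rule strips the questionnaire outcome of people who have both end-of-period questionnaires. The filter names diary data, and the next sentence gives the questionnaire and surveys a rule of their own ("data will only be analysed for participants for whom data are available for" both interventions). The reference to before enrolment looks like a drafting slip. The defect is that the set for the end-of-period questionnaire is unclear.
- That the contrast is biased as a matter of fact. The large figures need stopping to depend on symptoms and also to be four times as likely on one tint at an average score. Nothing in the document supports such an imbalance: the tints are masked, and the control is described as a similar colour unlikely to cause significant symptoms.

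The plan also has a comparison of the first tint alone, which needs no second period, and an unspecified sensitivity analysis whose content may sit in an analysis plan not shown. Whether the diary filter applies to the first-tint comparison is not stated, and the authors themselves describe it as low in power. These soften the point without answering it.

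**Conclusion.** The point holds in a limited form. The rule is stated in the protocol and is wrong as labelled: the set is complete pairs, and no stated analysis clearly recovers those lost. That conclusion needs no assumption.

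The consequence is conditional. The contrast is open to bias if loss depends on symptoms or tint. In the modelled cases the bias is nil under the null with equal stopping rules, and nil when stopping is unrelated to symptoms. It is a modest attenuation, to about 0.47 from 0.50, with equal symptom-related stopping of 5% to 10%. It is substantial (0.35, or 13% to 14% false positives under the null) only under the assumed 5%/20% imbalance. The direction depends on which tint loses more people. Whether non-wearers who keep diaries are excluded cannot be decided from the text and needs clarifying. Because the protocol states the rule, an analysis plan that followed it would inherit the error.

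**What to change.** 1. Define the primary set as all randomised participants, analysed by assigned sequence in the mixed model already planned. Count every diary day (diary outcome) and every end-of-period questionnaire (questionnaire outcome), whatever the wear.
2. Keep the set with two weeks on both tints as a sensitivity analysis, and call it complete pairs.
3. Reconcile the statistical methods section with the section on discontinuing interventions, so that it is explicit whether diary days without wear count.
4. Correct the sentence that applies the both-interventions rule to the questionnaire before enrolment, so that the set for the end-of-period questionnaire is clear.
5. Add a sensitivity analysis for data not missing at random.

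The cost is wording plus two sensitivity analyses, and the trial status section says that recruitment has not begun. The downside is real: single-period data rest on a missing-at-random assumption, and bias remains if people who stop the lenses also stop their diaries. Item 5 is there for that reason, and continued diary completion after wear stops matters more than the choice of model.
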